### Exercise Therapy and Self-Stretching

To ensure comparability, the exercise therapy and self-stretching relaxation training are fully standardized across both groups. The program consists of (1) cervical isometric exercises (flexion, extension, lateral flexion, and rotation, each held for 10 s, 10 repetitions per direction); (2) upper trapezius and levator scapulae self-stretching (30 s per muscle, 3 repetitions each); and (3) postural reeducation. This session is performed at each treatment visit and prescribed as a daily home program. Adherence to the home program is recorded in a self-reported log. Because the exercise component is identical for both groups, any between-group differences observed at the end of the trial can be attributed to the added Tuina or ESWT rather than to the exercise itself. In the primary analysis, group allocation will be the independent variable, and the exercise protocol is considered part of the standard background care that is balanced by randomization.

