### Study Design

This is a single-center, randomized, controlled, parallel-group, assessor- and analyst-blinded, superiority trial comparing Tuina therapy versus ESWT in patients with NNP. The trial will be conducted at the General Hospital of Ningxia Medical University. Eligible participants will be randomly assigned in a 1:1 ratio to either the Tuina group or the ESWT group. Both groups will receive their respective intervention in addition to standardized exercise therapy over a 4-week treatment period, followed by a 4-week follow-up (total study duration: 8 wk). The flowchart of the trial process is shown in Figure 2, and the trial period is shown in Figure 3.

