### Interventions

All interventions will be delivered over a 4-week treatment period, with follow-up assessments conducted 4 weeks after treatment completion. Both groups will receive the same standardized exercise therapy and self-stretching relaxation program. The Tuina group will additionally receive 3-step Tuina therapy, and the ESWT group will additionally receive ESWT. All procedures take place in the treatment room of the Department of Rehabilitation Medicine, General Hospital of Ningxia Medical University. In order to improve the compliance of the subjects, the subjects will receive treatment and related assessment and examination free of charge.

Participants will receive enrollment education on the importance of treatment compliance, appointment reminders 24 hours before each session, flexible scheduling with transportation subsidies, and a treatment log cosigned by the participant and practitioner after each session. Adherence will be monitored through (1) treatment logs cosigned by participant and practitioner after each session, (2) attendance recorded in case report forms, (3) home exercise logs reviewed weekly, and (4) appointment reminders sent 24 hours before each session. Nonadherence thresholds are predefined: participants missing more than 20% of scheduled sessions (ie, ≥3 Tuina sessions or ≥2 ESWT sessions) or completing less than 70% of the prescribed home exercise program will be classified as nonadherent. A per-protocol analysis will be conducted in addition to the intention-to-treat (ITT) analysis. Treatment parameters in the ESWT group will be randomly audited every 2 weeks to ensure protocol consistency.

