### Data Analysis

#### Analysis Populations

Three populations will be defined: the ITT population (all randomized, primary analysis), the per-protocol population (≥80% sessions completed and primary outcome assessed, sensitivity analysis), and the safety population (≥1 intervention received, safety analyses).

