This trial has several methodological limitations that should be acknowledged. First, owing to the nature of the interventions, participants and therapists cannot be blinded; this may introduce performance and expectation biases, which we have sought to mitigate through blinded outcome assessment, standardized information on treatment credibility, and analysis of blinding integrity. Second, the treatment session frequency differs between groups (12 Tuina sessions vs 7 ESWT sessions). This discrepancy reflects real-world clinical practice but could confound the estimated treatment effect; we plan to examine the influence of session attendance in sensitivity analyses and discuss it as a potential limitation. Third, the sample size (58 participants) was calculated to detect a large effect size; if the true between-group difference is smaller, the trial may be underpowered. Accordingly, treatment effect estimates and CIs will be emphasized over binary significance statements. Fourth, this is a single-center study, which may limit generalizability; a future multicenter trial would enhance external validity. Fifth, the 4-week follow-up period is relatively short and may not capture the long-term sustainability of treatment effects.

The findings of this trial are expected to provide comparative data that may inform clinical decision-making for individuals with NNP. If Tuina proves superior to ESWT in reducing pain and disability, its advantages of low equipment requirements and patient comfort could support its adoption as a preferred nonpharmacological treatment, particularly in settings with limited access to shock wave devices. Conversely, if Tuina does not demonstrate superiority, ESWT would retain its role as an evidence-based physical modality, while Tuina might still be considered a viable alternative, given its practical advantages, provided that its clinical effects are comparable. Regardless of the outcome, the trial will generate evidence on the differential effects of these 2 interventions on pain, function, muscle elasticity, and inflammatory biomarkers, contributing to more individualized treatment selection.

In conclusion, this protocol describes a methodologically rigorous randomized trial designed to address a specific evidence gap. The results, interpreted within the context of the acknowledged limitations, will contribute to the evidence base for nonpharmacological management of NNP.

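### The protocol rules out exercise as a cause of any group difference, but in-clinic exercise follows visit count (12 Tuina, 7 ESWT), which randomization cannot balance

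*Protocol article*

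**What the plan says.** The section Exercise Therapy and Self-Stretching describes one programme for both groups (isometric holds, stretches, postural work) and says how it is delivered: "This session is performed at each treatment visit and prescribed as a daily home program". It then draws an inference: "Because the exercise component is identical for both groups, any between-group differences observed at the end of the trial can be attributed" to Tuina or ESWT and not to exercise. For the primary analysis it treats the exercise protocol as "part of the standard background care that is balanced by randomization".

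Study Design describes the arms as each modality on top of exercise: "Both groups will receive their respective intervention in addition to standardized exercise therapy over a 4-week treatment period".

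The Abstract and the two treatment sections give Tuina three times a week for 4 weeks, and ESWT on days 1, 5, 10, 15, 20, 25 and 30.

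The Discussion lists as a limitation that "the treatment session frequency differs between groups (12 Tuina sessions vs 7 ESWT sessions", and comments: "This discrepancy reflects real-world clinical practice but could confound the estimated treatment effect". It plans sensitivity analyses of session attendance. It does not mention exercise there.

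**The concern.** To exclude exercise as a cause of any difference, the two groups must have equal exposure to exercise. Equal content per session is not enough. Here the number of in-clinic exercise sessions comes with the assigned treatment, so it differs by arm by design. Randomization balances, in expectation, what participants bring to the trial. It does not balance something the allocation itself determines.

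What is at stake is the conclusion the report may draw. If Tuina does better, the present wording would let the authors credit the manual technique alone. The design supports a comparison of Tuina with its 12 visit-linked exercise sessions against ESWT with its 7. The wording also sits badly with the Discussion, which accepts that the visit imbalance could confound the effect.

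**Working it through.** **Inputs**

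- Exercise is done at each treatment visit and also prescribed daily at home (Exercise Therapy and Self-Stretching).
- Tuina: 3 visits per week for 4 weeks (Abstract; Tuina Therapy).
- ESWT: days 1, 5, 10, 15, 20, 25 and 30 (Extracorporeal Shock Wave Therapy).
- Assumptions: home days number 28 or 30, there is at most one visit per day, and all 12 Tuina visits fall within 28 days. The article describes no exercise-only visits for the ESWT group; that there are none is inferred from its silence.

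**Step 1. Reproduce the stated visit counts.** Tuina: 3 × 4 = 12. ESWT: 7 listed days = 7. Both agree with the Discussion.

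**Step 2. In-clinic exercise sessions.** One per visit, so 12 and 7 in all: a difference of 12 − 7 = 5 and a ratio of 12/7 = 1.71. By day 28 the day-30 ESWT visit has not yet happened, so the counts are 12 and 6, ratio 12/6 = 2.0. Which pair applies to the week-4 endpoint depends on whether that assessment precedes the day-30 visit.

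**Step 3. Total prescribed sessions, under both readings of the delivery sentence.**

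| Reading | Window | Tuina | ESWT | Ratio |
|---|---|---|---|---|
| Clinic session adds to the home session | 28 days | 28 + 12 = 40 | 28 + 6 = 34 | 1.18 |
| Clinic session adds to the home session | 30 days | 30 + 12 = 42 | 30 + 7 = 37 | 1.14 |
| Clinic session replaces the home session | 28 days | 28 (12 clinic, 16 home) | 28 (6 clinic, 22 home) | 1.00 |
| Clinic session replaces the home session | 30 days | 30 (12 clinic, 18 home) | 30 (7 clinic, 23 home) | 1.00 |

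The text does not choose between the readings. Under the first, prescribed exercise differs by arm. Under the second, the total is equal and only the place differs, with home sessions tracked by a self-reported log.

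**Step 4. Set against the attribution statement.** Under either reading the in-clinic component differs by arm, so a claim covering any difference is not supported. Nothing in the document converts extra in-clinic sessions into VAS points, so no bias can be computed.

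**The case against.** The strongest reply is that the imbalance is already disclosed. The Discussion gives 12 against 7, calls it a possible confounder and plans attendance analyses. A reader who also knows that exercise happens at each visit can connect the two. Calling the programme identical can also be read as referring to content, which is indeed standardized, and the daily prescription is the same for everyone. On the replacement reading, even the total dose is equal.

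Much of this stands, and it is why the point is minor. It does not rescue the sentence. The limitation speaks of treatment session frequency and leaves the attribution statement unqualified. The attendance analysis cannot readily separate exercise from modality either, because the scheduled visit count is fixed by arm and each visit delivers both.

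Three stronger readings are tempting, and the document does not support them:

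- A reader might infer that the Tuina group is prescribed more exercise overall. That holds only if clinic sessions add to home sessions, which is not stated.
- A reader might infer a bias in favour of Tuina. The document gives no basis for the direction or size of any effect, and it never describes clinic exercise as supervised.
- A reader might see a further flaw in the per-protocol set. Nonadherence is defined as "participants missing more than 20% of scheduled sessions (ie, ≥3 Tuina sessions or ≥2 ESWT sessions", and the set requires at least 80% of "sessions completed and primary outcome assessed, sensitivity analysis". That leaves at least 10 Tuina visits (0.8 × 12 = 9.6) and at least 6 ESWT visits (0.8 × 7 = 5.6). This restates the schedule. The plan never claims that this set equalises visits.

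**Conclusion.** The statement is wrong as written, and the consequence is minor. Session content and the daily home prescription are the same. In-clinic exercise is not: 12 sessions against 7 in all, or 12 against 6 by day 28. It is set by arm, so it is neither identical nor balanced by randomization, and exercise cannot be excluded as a contributor to a group difference. Whether total prescribed exercise differs is open: equal on one reading, 40 against 34 or 42 against 37 on the other, assuming 28 or 30 home days.

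It would go too far to conclude that the trial's comparison is invalid. The intention-to-treat contrast remains a sound comparison of two regimens, which is how Study Design describes the arms. The sample size and the primary model are unaffected. Confidence is high about the wording and does not extend to any effect on VAS.

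**What to change.** Change wording only, and leave delivery as it is.

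1. In Exercise Therapy and Self-Stretching, replace the statements on identical exercise, attribution and balance by randomization with text such as: *Session content and the daily home prescription are the same in both groups; in-clinic exercise follows each group's visit schedule (12 Tuina visits; 7 ESWT visits, 6 of them by day 28), so the between-group contrast compares two regimens, each treatment with its visit-linked exercise.*
2. In the Discussion's limitation on session frequency, add that in-clinic exercise differs along with the visits.
3. Optionally, tabulate clinic and home exercise sessions by arm from the treatment and home exercise logs already kept.

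The cost is two short edits and, if wanted, one descriptive table. Visits, model and sample size stay the same. The price is a narrower conclusion, about regimens and not about the modality alone.

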**Methods:**

In this randomized, controlled, single-blind trial, 58 patients with NNP will be allocated in a 1:1 ratio into 2 groups: Tuina therapy and ESWT. The Tuina group will receive 30-minute sessions 3 times per week for 4 weeks (12 sessions total). The ESWT group will receive interventions on days 1, 5, 10, 15, 20, 25, and 30 (7 sessions total). The primary outcome measure will be pain intensity measured by the visual analog scale. Secondary outcome measures will include the Neck Disability Index, cervical active range of motion, shear wave elastography (SWE) using musculoskeletal ultrasound, and serum inflammatory factors. All outcome measures will be assessed at baseline, during treatment (2 and 4 wk), and at the 8-week follow-up, except for SWE and inflammatory factors. SWE will be measured at baseline, 4 weeks, and 8-week follow-up; inflammatory factors will be measured at baseline and 4 weeks.

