### Extracorporeal Shock Wave Therapy

ESWT will be performed using a Swiss Storz extracorporeal shock wave therapeutic apparatus (MP50). The MP50 device delivers radial (dispersive) shock waves, characterized by a divergent wave pattern that distributes energy over a broader, more superficial tissue area. Each session will deliver 2000 shocks at a pressure of 1.5 to 2.0 bar and a frequency of 10 to 12 Hz, with moderate handle pressure. Based on the pressure range and radial wave characteristics, the estimated energy flux density ranges from 0.10 to 0.20 mJ/mm², which falls within the medium-energy category as defined by international consensus guidelines (medium estimated energy flux density: 0.08‐0.28 mJ/mm²). The therapy will target tender points and the surrounding soft tissues. Treatment will be administered on days 1, 5, 10, 15, 20, 25, and 30.

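### The protocol rules out exercise as an explanation for a group difference, but in-clinic exercise follows the visit schedule: 12 sessions with Tuina, 7 with ESWT

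*Protocol article*

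**What the plan says.** Under Exercise Therapy and Self-Stretching, the protocol describes one standardized program for both arms and says how it is delivered: "This session is performed at each treatment visit and prescribed as a daily home program". It then draws two conclusions. The first is about attribution: "Because the exercise component is identical for both groups, any between-group differences observed at the end of the trial can be attributed to" whichever treatment was added, with exercise excluded. The second is that "the exercise protocol is considered part of the standard background care that is balanced by randomization".

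The number of treatment visits differs by arm:

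- Tuina (Abstract, Methods): "The Tuina group will receive 30-minute sessions 3 times per week for 4 weeks (12 sessions total").
- ESWT (Extracorporeal Shock Wave Therapy): "Treatment will be administered on days 1, 5, 10, 15, 20, 25, and 30", which is 7 visits.

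The limitations paragraph of the Discussion acknowledges the 12-versus-7 difference. It says the difference "could confound the estimated treatment effect; we plan to examine the influence of session attendance in sensitivity analyses" and will be discussed as a limitation. It does not mention exercise.

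**The concern.** The exercise content and the daily home prescription are the same in both arms. The in-clinic exercise session is not, because it takes place at treatment visits and the number of visits is part of the allocated regimen. Randomization balances, in expectation, what precedes allocation. It does not balance what allocation itself determines. The two conclusions in the exercise section therefore claim a property that the design does not have.

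What is at stake is interpretation. Read under the protocol's own rule, a week-4 difference in VAS or NDI would be credited to Tuina or to ESWT alone. The extra in-clinic exercise falls in the Tuina arm, which the Introduction hypothesizes to be superior. The Discussion would use a positive result to support Tuina as a preferred treatment.

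**Working it through.** **Inputs.** Tuina: 3 visits per week for 4 weeks (Abstract; Tuina Therapy). ESWT: days 1, 5, 10, 15, 20, 25 and 30 (Extracorporeal Shock Wave Therapy). One exercise session per visit plus a daily home program (Exercise Therapy and Self-Stretching). Adherence rules: Interventions and Analysis Populations.

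**Step 1: reproduce the protocol's visit counts.** Tuina: 3 × 4 = 12. ESWT: seven listed days = 7. Both match the 12 and 7 given in the Discussion.

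**Step 2: in-clinic exercise sessions, one per visit.**

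| Up to | Tuina | ESWT | Ratio |
|---|---|---|---|
| Day 14 | 3 × 2 = 6 | 3 (days 1, 5, 10) | 2.0 |
| Day 28 | 12 | 6 (day 30 not yet reached) | 2.0 |
| End of treatment | 12 | 7 | 12/7 = 1.71 |

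**Step 3: total prescribed exercise.** The protocol does not say whether a visit session adds to or replaces that day's home session. I assume a 28-day home program in both arms.

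- Additive: 28 + 12 = 40 versus 28 + 7 = 35, ratio 1.14. By day 28, 40 versus 28 + 6 = 34, ratio 1.18.
- Replacement: 28 versus 28 by day 28. Only the setting differs: 12/28 = 43% in clinic with Tuina, 6/28 = 21% with ESWT.
- Replacement with incomplete home exercise: the Interventions section accepts 70% home completion as adherent. As an illustration, assume full attendance and 70% completion on non-visit days. By day 28 that gives 12 + 0.7 × 16 = 23.2 versus 6 + 0.7 × 22 = 21.4 sessions.

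Equal delivered exercise is therefore not secured under either reading.

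**Step 4: can the attendance analysis separate exercise from treatment?** The Interventions section classes as nonadherent "participants missing more than 20% of scheduled sessions (ie, ≥3 Tuina sessions or ≥2 ESWT sessions"). Adherent participants therefore attend 12 − 2 = 10 to 12 Tuina visits, or 7 − 1 = 6 to 7 ESWT visits. The Analysis Populations section defines "the per-protocol population (≥80% sessions completed and primary outcome assessed, sensitivity analysis"), which gives the same limits: 0.80 × 12 = 9.6, so at least 10; 0.80 × 7 = 5.6, so at least 6. The lowest adherent Tuina count (10) exceeds the highest possible ESWT count (7), so the ranges do not overlap.

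Among nonadherent participants the counts can overlap. But each visit delivers both the treatment and the exercise, so within an arm the two rise and fall together. Attendance cannot tell them apart there either.

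**The case against.** The strongest reply has four parts.

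- **Disclosure.** The Discussion already states the 12-versus-7 difference and calls it a possible confounder, and in-clinic exercise happens at those same visits. This stands in part. But the Discussion never names exercise, and the categorical exclusion in the exercise section is left unqualified. The reader is given both a caveat and a denial.
- **Dose.** If visit sessions replace home sessions, the prescribed totals are equal, and nothing in the protocol says that clinic exercise is supervised or more intense. This also stands as a limit on size. The inequality in total prescribed sessions holds only on the additive reading, and the effect of setting is unknown. It does not rescue the statement as written, because the protocol never says which reading applies.
- **Attendance analysis.** The non-overlap applies only to adherent participants, while the planned analysis may use everyone. That is correct about the counts. The inseparability does not depend on the subset, because treatment and exercise share every visit.
- **Timing.** The count of 6 ESWT sessions assumes that the week-4 assessment precedes the day-30 visit, which the article does not settle. If it follows that visit, the contrast is 12 versus 7, and the argument is unchanged.

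It is also fair to say that Study Design and Interventions already describe each arm as its treatment in addition to exercise. That supports a comparison of packages, which is less than the exercise section claims.

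**Conclusion.** The point holds: the attribution and balance statements are wrong for the in-clinic part of the exercise program. Scheduled in-clinic exercise is 12 versus 7 sessions, and 12 versus 6 by day 28. Total prescribed sessions range from equal to 14% more with Tuina (18% counting to day 28), depending on a rule the protocol leaves open and on the assumed 28-day home program. The protocol gives no basis for turning this into VAS points, and I claim none.

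The practical effect may be modest. The intention-to-treat test of the two regimens, its error rate, the sample size and the primary model are unaffected. What changes is the permissible conclusion: the trial compares Tuina plus exercise at 12 visits with ESWT plus exercise at 7 visits. It should be corrected before analysis.

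**What to change.** 1. In Exercise Therapy and Self-Stretching, delete the attribution sentence and the statement about balance by randomization. Suggested replacement: *Exercise content and the daily home prescription are the same in both groups. Because the session is also carried out at every treatment visit, the number of in-clinic exercise sessions follows the treatment schedule: 12 with Tuina and 7 with ESWT.*
2. State whether a visit session replaces that day's home session or adds to it.
3. In the Abstract's Conclusions, Study Design and the Discussion, describe the comparison as one of two packages.
4. In the Discussion's limitation on session frequency, name in-clinic exercise and say that the attendance analysis cannot separate it from the allocated treatment.
5. Report in-clinic and home exercise sessions completed by arm.

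Do not equalize exercise visits now. By March 30, 2026, 26 of the 58 participants had been enrolled, and a change would split the cohort between two schedules.

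The cost is a wording amendment and one descriptive table from the treatment and home-exercise logs already kept. Endpoint, sample size, randomization, model and visits stay as they are. The price for the sponsor is a narrower claim: a difference could not be credited to Tuina or ESWT alone.
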